## Abstract

**Background:**

Chronic rhinosinusitis (CRS) is a common source of ill health; 11% of UK adults reported CRS symptoms in a worldwide population study. Guidelines are conflicting regarding whether antibiotics should be included in primary medical management, reflecting the lack of evidence in systematic reviews. Insufficient evidence to inform the role of surgery contributes to a fivefold variation in UK intervention rates. The objective of this trial is to establish the comparative effectiveness of endoscopic sinus surgery (ESS) or a prolonged course of antibiotics (clarithromycin) in adult patients with CRS in terms of symptomatic improvement and costs to the National Health Service compared with standard medical care (intranasal medication) at 6 months.

**Methods/design:**

A three-arm parallel-group trial will be conducted with patients who remain symptomatic after receiving appropriate medical therapy (either in primary or secondary care). They will be randomised to receive: (1) intranasal medication plus ESS, (2) intranasal medication plus clarithromycin (250 mg) or (3) intranasal medication plus a placebo. Intranasal medication (current standard medical care) is defined as a spray or drops of intranasal corticosteroids and saline irrigations. The primary outcome measure is the SNOT-22 questionnaire, which assesses disease-specific health-related quality of life. The study sample size is 600. Principal analyses will be according to the randomised groups irrespective of compliance. The trial will be conducted in at least 16 secondary or tertiary care centres with an internal pilot at six sites for 6 months.

**Discussion:**

The potential cardiovascular side effects of macrolide antibiotics have been recently highlighted. The effectiveness of antibiotics will be established through this trial, which may help to reduce unnecessary usage and potential morbidity. If ESS is shown to be clinically effective and cost-effective, the trial may encourage earlier intervention. In contrast, if it is shown to be ineffective, then there should be a significant reduction in surgery rates. The trial results will feed into the other components of the MACRO research programme to establish best practice for the management of adults with CRS and design the ideal patient pathway across primary and secondary care.

**Trial registration:**

ISRCTN36962030. Registered on 17 October 2018.

**Electronic supplementary material:**

The online version of this article (10.1186/s13063-019-3314-7) contains supplementary material, which is available to authorized users.

## Background

### Background and rationale

#### The problem being addressed

Chronic rhinosinusitis (CRS) is a common source of ill health; 11% of UK adults reported CRS symptoms in a worldwide population study [1]. Symptoms, including nasal obstruction, nasal discharge, facial pain, anosmia and sleep disturbance, have a major impact on quality of life (QoL), reportedly greater in several domains of the SF-36 than angina or chronic respiratory disease [2]. Acute exacerbations, inadequate symptom control and respiratory disease exacerbation are common. Complications are rare but may include visual impairment and intracranial infection. Longitudinal primary-care electronic health records from the Clinical Practice Research Datalink, a nationally representative subset of primary-care data across consenting general practices, show that 1% of UK adults receive treatment for CRS from their general practitioner (GP) each year, with a median of four GP visits. They receive multiple medications, with 91% receiving an antibiotic prescription [3]. Secondary-care electronic health records for 2012/13 from Hospital Episode Statistics, England’s national administrative billing dataset for hospitals, show that approximately 40,000 sinus operations were performed in England and Wales, in addition to an estimated 120,000 outpatient consultations [4]. A worldwide study demonstrated that one in three CRS patients in primary care have poorly controlled symptoms [5]. The socio-economic cost of CRS is significant, with 57% of patients reporting absenteeism and 28% experiencing associated anxiety and depression [6, 7]. US businesses report CRS as one of the top 10 illnesses that cause absence from work [8].

#### Need and rationale for research in this area

The European Position Paper on Rhinosinusitis and Nasal Polyps (EPOS 2012) includes treatment guidelines and a research strategy for CRS, emphasising where limited evidence restricts care [9]. Key elements of this strategy are addressed herein, including the paucity of randomised controlled trials (RCTs) of treatments for rhinosinusitis. In the UK, there are no specific national treatment guidelines and adherence to EPOS 2012 is variable [10]. A recent ENT-UK commissioning guideline [11] acknowledges the lack of high-quality trials and although it does not recommend routine antibiotic use for CRS in primary care, GPs often prescribe repeated courses [12], which may cause resistance. There is growing interest in the immune-modulating and anti-inflammatory effects of macrolide antibiotics in treating chronic airway inflammatory disease, with low-dose long-term macrolides being prescribed for their immune response and not primarily as anti-bacterial agents [13]. Longer-term antibiotic use in secondary care has a low-grade recommendation, reflecting conflicting evidence from two RCTs [14, 15], resulting in a call for further trials [16–18].

First-line therapy is often delivered in primary care, and consists of initial treatment with intranasal corticosteroids, short courses of antibiotics or saline rinses. At least one in three CRS patients attending ear, nose and throat (ENT) clinics are considered to have failed this initial treatment, which is known as appropriate medical therapy (AMT), and are considered for endoscopic sinus surgery (ESS) [19, 20]. Insufficient evidence to define the role of surgery contributes to a fivefold variation in intervention rates across England, as determined by the clinical commissioning group [11]. The duration of symptoms before surgery varies from under 1 to over 10 years [21, 22]. If surgery is less effective than AMT, patients may be exposed to unnecessary risks and morbidity. If surgery is more effective, current delays reflect suboptimal patient care. Such uncertainty resulted in the inclusion of ESS in the Database of Treatment Uncertainties (DUETS) of the National Institute for Health and Care Excellence (NICE) [23].

As the EPOS 2012 guidelines recommend AMT prior to surgery, any trial must ensure patients have failed to respond to an adequate attempt at treatment using AMT. Intranasal corticosteroids and saline irrigation, for which there are strong recommendations for use based on high-quality level 1 evidence, should be included in AMT. Guidelines are conflicting regarding whether antibiotics should be included in primary medical management, reflecting the lack of evidence noted above. Our trial uses a pragmatic approach in which eligibility for surgery is based on a shared decision between the principal investigator (PI) and the patient, after initial treatment with AMT, in keeping with current guidelines [9, 24, 25].

#### Past and current research

Cochrane reviews have recently been completed covering the treatment options being assessed in this trial [26–31]. They support the use of intranasal corticosteroids and saline irrigations as standard treatment but express the need for more trials with antibiotics. A systematic review of ESS commissioned by the Human Tissue Authority identified the need for high-quality studies comparing surgery with medical treatment [32, 33]. Updated reviews of the literature and trial registries have not identified new studies. One potentially relevant trial reported by DUETS was never started. Two 2014 Cochrane systematic reviews of medical and surgical management concluded that further studies are urgently needed [34, 35]. There is little ongoing research that overlaps with the MACRO programme. Two relevant antibiotic trials are currently recruiting. A trial aiming to determine the optimum duration of longer-term antibiotics in patients with CRS [36] compared the effectiveness of 3 with 6 weeks of azithromycin but did not include a placebo arm. A commercially sponsored study compared azithromycin with a placebo in patients with persistent symptoms after ESS [37], but for many patients the aim was to avoid primary surgery [38]. Therefore, a trial to determine the effectiveness of antibiotics compared with ESS is essential. Finally, an RCT comparing ESS with topical medical therapy versus topical medical therapy alone for a subgroup with CRS with nasal polyps (CRSwNPs) is underway in the Netherlands [39].

#### Importance of the research

Despite the burden of CRS, UK health-economic evaluations are lacking. An American model demonstrates a high economic burden to patients, health-care systems and society [40, 41]. In 2011, CRS cost the US health-care system $8.6 billion with significant direct and indirect costs. Antibiotic resistance is considered one of the most significant threats to patient safety in Europe [42]. Evaluating the effectiveness of antibiotics and promoting appropriate usage is integral to the UK 5-year antimicrobial resistance strategy [43]. Given the high prevalence of CRS and the variability in prescribing antibiotics, this may represent a public health danger through selective pressure on bacteria and antibiotic resistance. In addition, the potential cardiovascular side effects of macrolide antibiotics have recently been highlighted [44]. The effectiveness of antibiotics must be urgently established to reduce unnecessary use and potential morbidity. International guidelines suggest that patients should receive the ‘maximum medical therapy’, which usually includes nasal (and possibly oral) steroids, antibiotic treatment and regular nasal douching, prior to surgical intervention. However, the use and duration of antibiotic use is very variable. In total, 91% of CRS patients currently receive an antibiotic prescription prior to referral. Recently, some clinical commissioning groups have insisted on a 3-month trial of macrolide antibiotics prior to secondary-care referral [48]; however, evidence to support this recommendation is lacking.

There is both wide variation in surgical practice and very high rates of revision surgery [45, 46]. There is a risk that patients may undergo surgery and its attendant complications without due reason. In contrast, recent changes to commissioning that restrict access to sinus surgery may deny beneficial treatment to patients. The risk is that limited evidence for effectiveness is assumed to indicate non-effectiveness, leading to the decommissioning of an effective treatment by clinical commissioning groups, with some already deviating widely from NICE commissioning guidelines [47]. It is essential to assess rigorously the effectiveness and cost-effectiveness of surgery to enable robust decision-making from patient, health service and societal perspectives. In non-randomised studies, surgery achieves significant improvements in health-related QoL and reductions in ongoing health-care utilisation. Pre- and post-trial health economic modelling will ensure the trial design reflects current pathways. If ESS is clinically effective and cost-effective, the trial may encourage earlier intervention. In contrast, if it is shown to be ineffective, there should be significant reductions in surgery rates.

The MACRO trial forms part of a larger programme of work, the overarching aims of which are (1) to address the major deficiencies in the evidence base for CRS management, (2) to establish best practice for the management of adults with CRS and (3) to design the ideal patient pathway across primary and secondary care.

### Objectives

#### Primary objective

The primary objective is to establish the comparative effectiveness of a prolonged course of antibiotics (clarithromycin) or ESS in adult patients with CRS in terms of symptomatic improvements and costs to the National Health Service (NHS), compared with standard medical (intranasal medication) care at 6 months.

#### Secondary objectives

The secondary objectives are:To measure clinical effectiveness using subjective self-report ratings and objective clinical measuresTo compare the clinical effectiveness according to phenotype: CRS with and without polyps (CRSwNPs versus CRSsNPs)To record the incidence and details of adverse events (AEs) in all treatment arms that are related to the trial medication or surgery interventionTo establish the cost-effectiveness and cost utility of each arm relative to the others over the 6-month trialTo embed a mixed-methods evaluation into the main trial to identify factors and processes necessary in the implementation of the trial findings

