### Trial design

#### Overall design

The MACRO trial is a multi-centre three-arm placebo controlled parallel-group RCT that aims to randomise 600 adult patients with CRS. Patients who remain symptomatic after receiving AMT as deemed suitable by the local PI or co-investigator (Co-I) (either in primary or secondary care) and who are considered suitable candidates for further treatment (including surgery) will be randomised on a 1:1:1 basis to receive:Intranasal medication plus ESS within 6 weeks of randomisation (ESS group)Intranasal medication plus an initial 2-week course of capsules with 250 mg of clarithromycin twice daily followed by a 10-week course of capsules with 250 mg of clarithromycin once daily (antibiotic group)Intranasal medication plus an initial 2-week course of placebo capsules twice daily followed by a 10-week course of placebo capsules once daily (placebo group)

Intranasal medication (current standard medical care) is defined as a spray or drops of intranasal corticosteroids and saline irrigations as per local formulary guidelines. Saline rinses will be provided by a research nurse (RN). These are non-investigational medicinal products (NIMPs) (see Name and description of each NIMP).

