#### Blinding (masking)

Blinding of participants and medical staff will be maintained for the comparison of clarithromycin by using a placebo identical in appearance to the antibiotic, although the MACRO trial office can reveal the treatment allocation in case of clinical need. Participants and medical staff will not be blinded to receiving surgery. At the end of each trial participant’s follow-up period of 6 months, the participant will return to normal NHS care. Those who remain symptomatic at this point will receive further treatment as defined by their ENT clinician, which may include being offered steroids, antibiotics or ESS, depending on which arm of the trial they were in. Patients who were allocated to either the placebo or clarithromycin will not be told of their allocation at the end of their 6-month trial period, except in an emergency.

If there is a need to treat a patient in an emergency following a serious adverse reaction (SAR), the treating PI or medical doctor can break the code using the randomisation system to see if the patient was on the active drug. Under these exceptional circumstances, the PI or a member of the site team can unblind the participant using the clinical trial unit’s in-house RRAMP system. If unblinding is required for any other reasons apart from an emergency, site staff must submit a request (through RRAMP) and the request will be reviewed. If appropriate, it will be approved by a member of the central MACRO trial office. Where a SAR is not an emergency to treat but is deemed to be a suspected unexpected serious adverse reaction (SUSAR), then the clinical trial unit will break the code for reporting purposes without necessarily involving the PI. If on breaking the code it is found that the patient was actually taking the placebo, the event will not be classed as a SUSAR.

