### Statistical methods

#### Statistical analysis

Full details of the statistical analysis plan will be agreed by the MACRO programme steering committee (PSC) before the data are unblinded. A summary of the planned analyses is presented here. The primary analysis will be according to the randomised allocation, irrespective of subsequent treatment compliance, and conducted at the two-sided 5% significance level with 95% confidence intervals. No adjustment for multiple comparisons is planned, as the comparisons relate to distinct clinical decisions (use or non-use of an antibiotic and surgery versus medical management of one form). Baseline data and participant flow information will be summarised without a formal analysis. The primary outcome will be analysed using linear regression adjusted for baseline SNOT-22 and also for the presence or not of polyps at baseline. Clustering by surgeon will also be accounted for where relevant using an appropriate method (e.g. the cluster robust option in Stata). Secondary outcomes will be analysed similarly using generalised linear models.

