### Harms

The sponsor’s responsibility for pharmacovigilance has been delegated to SITU within OCTRU, University of Oxford. The severity of AEs (for either IMP or ESS) will be classified as mild (1), moderate (2) or severe (3), as described in Table 1.

**Table 1 Tab1:** Categories for adverse events

Category	Definition
Mild	The adverse event does not interfere with the participant’s daily routine and does not require intervention; it causes slight discomfort
Moderate	The adverse event interferes with some aspects of the participant’s routine or requires intervention, but is not damaging to health; it causes moderate discomfort
Severe	The adverse event results in an alteration, discomfort or disability that is clearly damaging to health

If an event satisfies the definition of a SAE, the PI, Co-I, RN or RP should complete a paper SAE form. The following information will be recorded: description, date of onset and end date, severity, assessment of causality due to trial medication or ESS, other suspect drug or device, and action taken. Follow-up information should be recorded as necessary. Trial visits and hospitalisation as part of standard clinical care will not be reported as an SAE, unless the hospitalisation extends beyond the expected length. SAE forms must be sent via secure email to [contact] within 24 h of the local trial team becoming aware of the event.

Any SAE or any AE that is more severe than would be expected that is considered related to the trial medication or surgery intervention, as judged by a medically qualified investigator, will be followed, either until resolution or the event is considered stable.

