#### Events related to the IMP

The most frequent and common adverse reactions related to clarithromycin therapy for adults are:Abdominal painDiarrhoeaNauseaVomitingDysgeusiaHeadacheInsomniaDyspepsiaRashHyperhidrosisAbnormal liver function test

These adverse reactions are usually mild in intensity and are consistent with the known safety profile of macrolide antibiotics. AEs will be recorded in the hospital notes in the first instance. The clinical symptoms of all AEs will be recorded, accompanied by a simple and brief description of the event, including dates as appropriate.

Any AE or adverse reaction that occurs after the baseline assessment (whether as would be expected, more severe than would be expected or unexpected) should be recorded. If an event is deemed to be more severe than would be expected, the PI, Co-I, RN or RP must complete an AE CRF, otherwise it should be detailed in the follow-up CRF at the 3- or 6-month clinic visit when the patient is seen by the PI, Co-I, RN or RP.

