#### Events related to ESS

The following AEs are possible following ESS:Post-operative bleeding needing nasal packing or readmission (1 in 200)Post-operative infection requiring antibiotics (1 in 15)Bruising around the eye (1 in 500)Leakage of cerebrospinal fluid (due to damage to the skull base, which may lead to meningitis) requiring repair, either at the time of surgery and delaying the patient’s discharge or later and causing a re-admission (1 in 1500)Major orbital injury leading to double vision or blindness (<1 in 10,000)

These events, and all other events relating to the ESS, will be recorded on the post-procedure CRF. Events occurring after the baseline assessment should be detailed in the 3- and 6-month post-randomisation follow-up visit CRF by the PI, Co-I, RN or RP.

Any leak of cerebrospinal fluid leading to meningitis (and hospitalisation) or major orbital injury leading to double vision or blindness must be recorded as an SAE. A delayed discharge for participants undergoing ESS will not be considered an SAE if the participant’s hospital stay is less than 24 h.

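### The harms outcome counts only adverse events attributed to treatment; all-cause events by randomised arm would give a like-for-like comparison at little cost

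*Protocol article*

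**What the plan says.** All references are to the protocol article.

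- **Secondary objectives.** The harms objective is to record the "incidence and details of adverse events (AEs) in all treatment arms that are related to the trial medication"; the sentence goes on to include events related to the surgery. The **Outcomes** section lists the matching secondary outcome, also restricted to events due to treatment.
- **Statistical analysis.** "Secondary outcomes will be analysed similarly using generalised linear models". No exception is made for adverse events.
- **Harms.** For the follow-up of serious events, and of events more severe than expected, relatedness means "considered related to the trial medication or surgery intervention, as judged by a medically qualified investigator".
- **Blinding (masking).** "Participants and medical staff will not be blinded to receiving surgery". For the other pair, "Blinding of participants and medical staff will be maintained for the comparison of clarithromycin by using a placebo identical in appearance to the antibiotic".
- **Events related to the IMP.** "Any AE or adverse reaction that occurs after the baseline assessment" should be recorded, whether or not it was expected.
- **Events related to ESS.** After listing procedural complications with their frequencies: "These events, and all other events relating to the ESS, will be recorded on the post-procedure CRF". The next sentence sends events after baseline to the 3- and 6-month follow-up forms.
- **Overall design.** The surgical arm is defined as "Intranasal medication plus ESS within 6 weeks of randomisation (ESS group"). It takes no capsules.

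**The concern.** A randomised comparison of harms does not need anyone to decide what caused each event: an excess in one arm over another is the evidence. Here the only stated adverse event outcome admits an event after a causal judgement, and the general sentence on secondary outcomes places it under between-arm models.

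Two consequences follow. Against ESS, the judgement is made openly and the arms have different things to attribute an event to, so the counts are not of the same kind of event. Between clarithromycin and placebo, where blinding makes an all-event comparison straightforward, the filter removes drug effects that the investigator took to be coincidental. The article itself highlights possible cardiovascular effects of macrolides (Abstract; Importance of the research; Dose modifications), and such events may well be judged unrelated.

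The trial is meant to inform both antibiotic use and surgical commissioning, so the harms comparison matters for each.

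**Working it through.** The plan gives no harms effect size, background event rate or harms test, so there is no figure of its own to reproduce. The check sets the sections side by side and adds two short calculations.

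**1. What is recorded against what is counted.** The section on events related to the investigational medicinal product (IMP) asks for any event after baseline. The objective and outcome count only attributed events, so the outcome is narrower than the recording. It is also unclear whether the recording is the same in every arm: the all-event sentence sits under a heading about the IMP, while the post-procedure form covers events relating to ESS. The follow-up form sentence in the ESS section suggests all-event recording there too, but does not say so outright.

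**2. Routes into the outcome, by arm.**

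| Arm | Capsule-related | Surgery-related | Intranasal-related |
|---|---|---|---|
| ESS, operated | no | yes | unclear |
| ESS, waiting or never operated | no | no | unclear |
| Clarithromycin | yes | no | unclear |
| Placebo | yes | no | unclear |

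The last column is unclear because the objective does not define trial medication. All arms use intranasal products, and the visit schedule's description of the weekly questionnaire groups them with the capsules as trial-specific medication. The second row exists because the Treatment schedule does not treat surgery after 6 weeks as non-compliance, and Stopping trial treatment keeps participants in follow-up if surgery does not go ahead.

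**3. Does the ESS arm contribute events?** Inputs: 600 participants at 1:1:1, so 200 per arm, and the frequencies listed under Events related to ESS. Assuming all 200 are operated on:

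200 × (1/15 + 1/200 + 1/500 + 1/1500) = 13.3 + 1.0 + 0.4 + 0.1 ≈ 14.9 events.

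Major orbital injury, at under 1 in 10,000, adds less than 200/10,000 = 0.02. So about 15 listed events would qualify, nearly all of them post-operative infection.

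**4. Direction in the ESS contrasts.** Consider a background symptom such as headache, equally common in every arm. Its reported difference between placebo and ESS is the background rate multiplied by (share attributed to a capsule in placebo − share attributed to surgery in ESS). The document gives neither share. If staff readily blame capsules, the filter favours ESS; if they readily blame a recent operation, it counts against ESS.

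**5. The blinded pair.** Let b be the background rate in both arms, d the true excess on clarithromycin, s_b the share of background events attributed and s_d the share of excess events attributed.

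- Reported placebo rate: s_b × b
- Reported clarithromycin rate: s_b × b + s_d × d
- Reported difference: s_d × d

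With d = 0 the difference is zero, so nothing spurious is created. With d above zero, the absolute difference shrinks by the factor s_d. For an assumed d of 10 percentage points, it stays at 10 if s_d = 1, falls to 5 if s_d = 0.5, and vanishes as s_d approaches 0. The risk ratio is unchanged only if s_d equals s_b.

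**The case against.** The strongest reply is that the objective's verb is to record, next to other objectives that do speak of comparing; that no harms test is described; and that the layout of adverse event tables normally belongs to the statistical analysis plan, which is not shown. It is true that no specific harms test is set out. But the restriction is written into a stated objective and outcome, and an analysis plan that follows them would carry it forward. The point is about what the article fixes, not about detail it leaves out.

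Four stronger readings are tempting, and the document does not support them.

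- A reader might infer that all arms are compared on unblinded attribution. Participants and medical staff are blinded for clarithromycin versus placebo; only the ESS contrasts are open.
- A reader might infer that ESS participants cannot contribute events, so that the arm would show an artificial zero. The objective includes surgery-related events, the article's own rates imply about 15 of them, and intranasal products may count as trial medication.
- A reader might infer that the bias favours ESS. Open attribution could equally assign background symptoms to the operation.
- A reader might infer that serious events judged unrelated, such as cardiac ones, go unreported. Under Harms, any event meeting the serious definition gets a form, on which causality is a field and not an entry condition. Deaths are notified separately, and the data safety monitoring committee reviews safety data. Such events would be missing from the attributed outcome, not from safety reporting.

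**Conclusion.** The point holds in a limited form. The only stated adverse event outcome depends on attribution. For the ESS contrasts that attribution is open and runs through different routes in different arms, so the comparison is not like for like. Neither the direction nor the size of any resulting bias can be derived from the document.

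For clarithromycin versus placebo, the cost is a smaller absolute difference, by the share of true drug events attributed. The move from 10 to 5 points illustrates an assumed one-half share and is not an estimate for this trial. The conclusion that no spurious difference arises assumes that blinding holds, so that background events are attributed equally in both arms.

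Because the wider data appear largely to be collected already, this is a cheap improvement and not a flaw that undermines the trial.

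**What to change.** 1. In Secondary objectives and Outcomes, define the safety outcome as all adverse events and all serious adverse events from randomisation to 6 months, presented by randomised arm regardless of attributed cause.
2. Reconcile Events related to the IMP with Events related to ESS: state that recording of any event after baseline applies identically in all three arms, asked for in the same way at the 3- and 6-month visits.
3. Keep investigator-judged relatedness and the procedural complications as descriptive breakdowns, and say whether trial medication includes the intranasal products.

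The visits and forms already exist, so the cost is wording, a few more tables and possibly a clarification to the case report form. The downside is that more background events will appear in the tables.
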